**Method:**

After the first visit to the dietician during which a detailed dietary history is taken, all included obese pregnant women will be telephone randomised 1:1:1, to intervention groups 1, 2 or to general standard regimen for all obese pregnant women as given above.

**Intervention aim:** Weight gain: <5 kg

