**Method:**

A detailed dietary history (360 questions) will be taken at the beginning and end of pregnancy using a questionnaire used and validated in the study “Better health for mother and child”(The Danish National Birth cohort). Importance of changes in the individual elements of the diet for the increase in maternal weight, fetal weight, length of pregnancy and pregnancy complications will be analysed.

Collection and analysis of date will be done in association with statisticians at Statens

Seruminstitut (the State Serum Institute).

**Calculation of strength in part-project B:** With an expected middle value for cholesterol of 270 mg/dl in week 37, with a standard deviation of 40 mg/dl (25), 129 women are needed in each group to detect a 5% reduction in cholesterol (alfa = 0.05: beta = 0.20). This number with a strength of 65% and an alfa of 0.05 will determine a 50% increase in pregnancy complications (prerequisite 25% pregnancy complications.) We aim to include 140 in each group in order to allow for any dropouts, **thus a total of 420 women**.

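### The 129 per group for cholesterol and the 65% power for complications rest on different meanings of alpha 0.05; on the two-sided basis that yields 129, the power for complications is about 58%

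*Protocol*

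**What the plan says.** The calculation is the last paragraph under Method in part B of the protocol (the questionnaire study), headed as the strength calculation for part-project B.

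- **Cholesterol.** It assumes an "expected middle value for cholesterol of 270 mg/dl in week 37, with a standard deviation of 40 mg/dl", sets "alfa = 0.05: beta = 0.20", and concludes that "129 women are needed in each group to detect a 5% reduction in cholesterol".
- **Complications.** The next sentence reuses that number: "This number with a strength of 65% and an alfa of 0.05 will determine a 50% increase in pregnancy complications". The base rate follows in brackets: "prerequisite 25% pregnancy complications".
- **Target.** The aim is 140 per group, 420 in all, to allow for dropouts.

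Allocation is set in part A, under Method: women are "telephone randomised 1:1:1, to intervention groups 1, 2 or to general standard regimen". A comparison of any two groups is therefore 1:1. The paragraph does not say whether either calculation is one- or two-sided, which test is meant, or whether a continuity correction was used.

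**The concern.** Two power statements stand side by side, share one sample size and carry the same alpha of 0.05. A reader will take them to rest on the same convention. The usual two-sided calculation does not return 65% for the second statement, and the one-sided calculation that does return it does not return 129 for the first.

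This is the only power figure the protocol gives for a clinical outcome; the other powered variable is cholesterol, and lipid profile is a secondary endpoint. Read as two-sided, the 65% implies a 35% chance of missing the stated difference, whereas the two-sided calculation gives about 42%. The 65% is also not comparable with the 80% in the sentence before it if the two use different tests.

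**Working it through.** **Inputs** (all from the strength paragraph except allocation, which is in part A, Method): n = 129 per group; alpha = 0.05; base rate p1 = 0.25; a relative increase of 50%, so p2 = 0.25 × 1.5 = 0.375; cholesterol mean 270 mg/dl and SD 40 mg/dl; a 5% reduction, 0.05 × 270 = 13.5 mg/dl; power 80% for cholesterol; 1:1 between any two groups.

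**Step 1. Reproduce the 129.** n per group = 2 × SD² × (z_alpha + z_beta)² / d², with z_beta = 0.842 and z_alpha = 1.960 (two-sided) or 1.645 (one-sided).

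| Difference d | Two-sided n | One-sided n |
| --- | --- | --- |
| 13.5 mg/dl | 137.8, so 138 | 108.6, so 109 |
| 14 mg/dl (13.5 rounded) | 128.1, so **129** | 100.9, so 101 |

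The 129 appears only two-sided, with the difference rounded to 14.

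**Step 2. Reproduce the 65%.** Mean proportion = (0.25 + 0.375)/2 = 0.3125.

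- SE under the null: SE0 = √(2 × 0.3125 × 0.6875 / 129) = 0.0577
- SE under the alternative: SE1 = √((0.25 × 0.75 + 0.375 × 0.625) / 129) = √(0.4219/129) = 0.0572
- Power = Φ((0.125 − z_alpha × SE0) / SE1). With continuity correction, 1/129 = 0.0078 is first subtracted from 0.125.

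| Test at 129 per group | Two-sided 0.05 | One-sided 0.05 |
| --- | --- | --- |
| Normal, uncorrected | Φ(0.208) = 58.2% | Φ(0.526) = 70.0% |
| Normal, continuity-corrected | Φ(0.072) = 52.9% | Φ(0.390) = **65.2%** |
| Fisher, by enumeration | 53.5% | **65.4%** |

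Solved for n, the one-sided continuity-corrected formula at 65% power gives 128.45, which rounds up to 129. So the protocol's figure can be reproduced, but only one-sided and with a conservative test.

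**Step 3. Other two-sided methods.** The unpooled variance gives 58.9%, the arcsine formula 58.5%, and exact enumeration of the uncorrected chi-square test 58.8%. None comes near 65%.

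**Step 4. Other readings, two-sided.**

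- All 140 per group analysed: 61.8%.
- The unrounded cholesterol number, 138 per group: 61.1%.
- A fall from 25% to 12.5% at 129 per group: 73.2% (67.7% corrected).
- An odds ratio of 1.5, that is 25% v 33.3%: 31.2%.
- The two intervention groups pooled against one, 258 v 129: about 70 to 72%.

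None gives 65%.

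**Step 5. What 65% would require on a two-sided test.** It needs 150.8, so 151, per group uncorrected, or 167 with continuity correction. With 129 per group, uncorrected, 65% is reached at about 25% v 38.6%, a relative increase of 0.386/0.25 − 1 = 54%.

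**Step 6. Put the two figures together.**

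| Convention for both | Cholesterol n | Complications power at 129 |
| --- | --- | --- |
| Two-sided | 129 (d = 14) or 138 (d = 13.5) | 53 to 59% |
| One-sided | 101 (d = 14) or 109 (d = 13.5) | 65% (corrected or Fisher) or 70% (uncorrected) |

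Neither row contains both 129 and 65%.

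**The case against.** A reader might infer that the 65% is simply an arithmetical error. The protocol does not support that. It states no sidedness, and two standard one-sided procedures return 65% at 129 per group, one of them returning exactly 129 when solved for n. The hypotheses in parts A and B are also worded in one direction, which makes a one-sided calculation conceivable. Overwriting 65% with 58% without asking could therefore replace a figure that is correct on the sponsor's own basis. The power for complications did not set the sample size, and both 58% and 65% fall openly short of the 80% used for cholesterol.

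Most of this stands, and it limits the point to inconsistency. It does not remove it. The one-sided reading that rescues the 65% does not yield the 129 in the sentence before, and no one-sided test is declared anywhere in the protocol. The directional wording is weak support, because the hypotheses predict reductions while the power sentence speaks of an increase. Nor is this detail that can wait for an analysis plan: the protocol itself states the sample size, rate, effect, alpha and power.

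**Conclusion.** The point holds as an inconsistency between two adjacent calculations. The 129 fits a two-sided test and the 65% fits a one-sided test with continuity correction or Fisher, although both are labelled alpha 0.05. On the two-sided basis that yields 129, power for 25% v 37.5% is about 58% uncorrected, some 7 percentage points below the stated 65%, or about 53% with continuity correction or Fisher. With all 140 per group analysed it is about 62% uncorrected.

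This rests on three assumptions: the 50% increase is relative; the comparison is between two groups of equal size; and the 129 came from rounding 13.5 to 14 mg/dl. If the last is wrong, the 129 has no basis on either convention tried here, and the two-sided power at 129 is unchanged. That the 65% is false on any reading is not shown. The consequence is modest: one stated figure needs correcting or explaining, and the design is unaffected.

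**What to change.** State the sidedness once, for both calculations, and name the test and any continuity correction.

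- **If two-sided:** replace 65% with about 58% for 129 analysed women per group (about 62% if all 140 are analysed; about 53% at 129 if the test is continuity-corrected or Fisher). Alternatively, keep 65% and state the difference it corresponds to at 129 per group, about 25% v 38.6%.
- **If the 65% was meant as one-sided, corrected or Fisher:** say so, give the two-sided power beside it, and reconcile it with the cholesterol sample size, which on a one-sided test would be 101 to 109.
- **In either case:** state whether the cholesterol difference was taken as 13.5 or 14 mg/dl.

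The cost is a sentence or two in one paragraph and, on the two-sided basis, a slightly less favourable power figure. No change in enrolment is needed.

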**ETHICAL CONSIDERATIONS:**

There is no risk or side effects associated with participation in the project . It is expected that the women randomised to intervention will have a reduced risk of developing pregnancy and labour complications and that the results can be expected to be important for the future treatment of obese pregnant women.

Positive as well as the negative results will be published in a scientific medical journal.

The project will be reported to Datatilsynet (Danish Data Protection Agency) and the medical ethics committees.

**ECONOMY:**

A sum of 300,000 DKK will be donated to the project by Sygekassernes helsefond. Money will also be sought from several funds. Neither the project leader nor others involved in the project group have any economic relation with Sygekassernes Helsefond, or any other possible contributors.

Participants will receive no economic compensation.
